# Pre-SAFEx: protocol for a single-centre, randomised, unblinded feasibility trial of Simultaneous Application of Flow at Extubation (SAFEx) in patients requiring intubation and ventilation for the management of acute respiratory failure

**DOI:** 10.1186/s40814-026-01817-7

**Published:** 2026-04-08

**Keywords:** Acute respiratory failure, Failed extubation, High-flow nasal therapy, Electrical impedance tomography, Critical care

## Abstract

**Background:**

Failed extubation within critical care is associated with increased morbidity and mortality. Although the role of high-flow nasal therapy (HFNT) has been established post-extubation, it is not clear whether the delay in establishing HFNT after extubation adversely affects lung physiology, resulting in an increased risk of extubation failure. Early administration of HFNT may prevent lung derecruitment and reduce the rate of extubation failure. Electrical impedance tomography (EIT) is a non-invasive, non-ionising imaging method that allows continuous real-time measurement of lung physiology.

**Methods:**

This is a single-centre, unblinded, randomised feasibility trial. Patients who have required intubation and ventilation for the management of acute respiratory failure will be recruited from the critical care unit at Queen Elizabeth University Hospital, Glasgow, Scotland. At the time of their planned extubation, patients will either be randomised to SAFEx extubation (where HFNT is established pre-extubation) or to standard care (where low-flow conventional oxygen therapy is established post-extubation). EIT will be used to compare the lung physiology of these two extubation strategies.

**Discussion:**

This randomised feasibility trial will provide the relevant information to determine whether a multi-centre feasibility study comparing a SAFEx extubation against standard care is viable. It will also determine the feasibility of using EIT as a measure of changes in lung physiology peri-extubation. As extubation failure remains a significant burden for critical care services, with an associated lack of evidence addressing the impact that the oxygen delivery device has on the outcome of extubation in high-risk patients, this study aims to take the first step in addressing this important research question.

**Trial registration:**

ClinicalTrials.Gov. Registration number: NCT05904652. Date of registration: 2023-06-15. https://clinicaltrials.gov/

## Background

Failed extubation is defined as the need for reinstitution of ventilatory support within 24 to 72 h of a planned extubation [1]. The mean rate in one review of interventional and observational studies was 15.7%, but this rate may be greater in high-risk patients [2]. Reintubation is associated with increased mortality [3]. Patients tend to be older, have pneumonia as an underlying diagnosis, have a more severe illness and are more likely to have a more rapid shallow breathing index [3].

High-flow nasal therapy (HFNT) was first described in the 1950s, but systems to deliver both heated and humidified oxygen at gas flows of up to 60 L/min have only been established in the past 15 years [4]. Greater oxygenation is achieved with high-flow devices in respiratory failure patients by better matching the patient’s peak inspiratory flow rate [5, 6]. This results in lower entrainment of and dilution with room air, resulting in more oxygen reaching the alveoli [7]. Another important mechanism is the generation of 3–5 cm H_2_O of positive end-expiratory pressure (PEEP) at flow rates of 30–50 L/min [7]. Humidification aids mucociliary function and secretion clearance and results in high tolerability [6]. There are a wide range of uses for the therapy. Most significantly, a mortality benefit has been demonstrated with its use in acute hypoxaemic respiratory failure [8].

Compared with conventional oxygen therapy, extubation of a patient onto a HFNT results in better oxygenation for the same inspired oxygen concentration after extubation and is associated with better comfort, less desaturation, and a lower reintubation rate [9, 10]. Moreover, in mechanically ventilated patients at high risk of extubation failure, the use of HFNT oxygen with non-invasive ventilation immediately after extubation significantly decreases the risk of reintubation compared with the use of HFNT alone [11]. 

Although the role of HFNT is established post-extubation, it is not clear whether the delay in establishing the therapy after extubation affects lung physiology, leading to an increased risk of reintubation. To characterise peri-extubation changes in lung aeration, two principal imaging modalities have been employed in the literature: lung ultrasound and electrical impedance tomography.

Lung ultrasound (LUS) enables serial assessment of lung aeration when performed using a standardised regional examination and reporting system for 12 regions, allowing aeration to be expressed semi-quantitatively as a score. Four ultrasound patterns reflect progressively worsening aeration loss: normal aeration with A-lines, moderate loss with well-separated B-lines, severe loss with coalescent B-lines, and complete loss with consolidation. An aeration score (0–36) is calculated by summing regional scores based on the worst pattern observed, with increasing scores indicating worsened aeration [12].

In a prospective observational study conducted in two multidisciplinary ICUs, Soummer et al. evaluated whether lung ultrasound score (LUS) could predict post-extubation distress by detecting impaired baseline aeration or derecruitment during a spontaneous breathing trial (SBT). SBTs were performed using a T-piece trial, and patients who passed were extubated. Among 100 mechanically ventilated patients, 86 were extubated after a successful SBT, of whom 34% developed post-extubation distress. In this heterogeneous patient group, higher baseline LUS and greater increases in LUS during the SBT were associated with post-extubation respiratory distress and an increased need for reintubation [13].

Electrical impedance tomography (EIT) is a non-invasive, real-time imaging modality that generates cross-sectional images of pulmonary ventilation. The technique measures changes in lung tissue impedance by applying small alternating electrical currents through skin surface electrodes and recording the resulting voltage differences [14]. The electrical currents emitted by EIT electrodes are inconsistently attenuated in different tissue types. Well-ventilated lung regions demonstrate higher impedance values, whereas poorly ventilated regions exhibit lower values, and unventilated areas demonstrate a minimum impedance value. Although conceptually analogous to computed tomography in generating cross-sectional images, EIT provides continuous, radiation-free bedside monitoring and reflects real-time changes in pulmonary physiology during inspiration and expiration [15].

EIT offers several advantages over lung ultrasound. First, EIT enables continuous data acquisition at up to 50 frames per second, allowing dynamic assessment of pulmonary function before, during and after extubation [16]. In contrast, lung ultrasound provides operator-dependent snapshot measurements. Calculation of a Lung Ultrasound Score (LUS) requires substantial training and expertise, may take up to 15 min to complete and may be susceptible to inter-observer variability [12].

Furthermore, EIT provides both global and regional information on pulmonary physiology down to the level of individual pixels. Functional EIT imaging enables assessment of clinically relevant physiological parameters, including regional ventilation distribution and changes in lung aeration, which are directly pertinent to evaluating lung recruitment peri-extubation [15].

Longhini et al. conducted a multicentre observational study examining changes in lung aeration and ventilation during the first spontaneous breathing trial (SBT) and following extubation in adult ICU patients at increased risk of extubation failure, using electrical impedance tomography (EIT). They found that SBT failure was associated with greater lung derecruitment, worsening oxygenation, and increased ventilation inhomogeneity; however, EIT-derived variables did not significantly differentiate between patients who ultimately succeeded or failed extubation. In this study, patients were extubated following a SBT to a Venturi mask, with CPAP or non-invasive ventilation used as rescue therapy where required [17].

### Study rationale

The patient’s respiratory function should be optimised prior to extubation, as reintubation is associated with increased morbidity and mortality. A strategy that best maintains lung recruitment and aids mucociliary function may reduce failed extubation. Conventional extubation strategies inevitably result in a delay between removal of the endotracheal tube and commencement of either high-flow therapy or low-flow oxygen. Although this period is relatively short, this could lead to aeration changes or derecruitment.

We propose to commence HFNT in patients who are receiving low respiratory support and who, in the opinion of the treating clinician, are deemed ready for extubation. The cuff on the endotracheal tube will remain inflated, and HFNT will commence gradually to achieve a flow of 60 L/minute, allowing humidification of the upper airway. Using EIT, this strategy of extubation with HFNT running will be compared with conventional oxygen therapy being commenced after extubation.

## Methods and analysis

### Study design and setting

The study is a single-centre, unblinded, randomised, feasibility trial. The study protocol was developed in accordance with the Standard Protocol Items: Recommendations for Interventional Trials (SPIRIT) 2013 Statement [18]. It is being carried out at the Queen Elizabeth University Hospital, Glasgow, UK—a tertiary centre and teaching hospital.

### Participant selection

Patients with respiratory failure of  ≥ 48 h who are scheduled for a planned extubation will be screened in critical care.

Written informed consent will be obtained from all patients recruited for the study. Consent will be sought directly from the patient where possible or from their Nearest Relative/Guardian or Welfare Attorney (or nearest ward if no suitable Nearest Relative/Guardian or Welfare Attorney is available) in accordance with the Adults with Incapacity (Scotland) Act 2000 for adults who lack capacity. Trial participants will be informed once they have recovered capacity after extubation that they are free to withdraw from the study at any time, without having to give a reason, and without their current or future care being affected. Written consent will be obtained to allow them to continue in the study.

### Study sample

In planning our feasibility study, we conducted a calculation to determine the required sample size for a future definitive randomised trial of SAFEx management versus standard care using G*Power software [19]. This was based on a 2-group Wilcoxon-Mann-Whitney test. We assumed a logistic distribution for the dependent variable (extubation failure rate) in this future trial, with an effect size of 0.1, an α error probability set at 0.05, and a desired power of 0.80 under a 1:1 randomisation scheme. This calculation suggested a total sample size of 2258 patients (1129 per group) would be required, indicating the need for a multi-centre trial.

We also referred to the work of Teare et al. [20], in which they explore the disagreement that currently exists within the literature over what sample size should be chosen for external pilot trials that inform the design of definitive randomised controlled trials. In their computer-based simulation study, Teare et al. [20] wished to provide recommendations on the required sample size for external pilot randomised controlled trials to enable the estimation of critical parameters that are necessary to inform the design of definitive randomised controlled trials (such as consent rate, event rate and attrition rate) with a reasonable degree of precision whilst avoiding over-recruitment. Their computer-programmed statistical illustration assessed multiple binary outcome success probabilities against a range of sample sizes. They concluded that a target sample size in the range of 60–100 patients per group (120 to 200 patients in total) was adequate.

For this feasibility study, we have chosen a recruitment target of 30 patients over 12 months. This is a pragmatic decision and has been driven by the limited resources we have to carry out this initial pilot. These include limits in staffing (with recruitment being facilitated by a single staff member working part-time), having access to a single Enlight 2100 electrical impedance tomography system and an uncertain local prevalence of eligible patients.

The extubation failure rate in the critical care sub-population with primary acute respiratory failure is not well defined. One review of the literature reports a mean extubation failure rate across all critical care patients of 15.7%, though this is likely to be greater in high-risk groups such as those with acute respiratory failure [2]. With the intervention being considered in this study, we would consider an absolute risk reduction in extubation failure rate of 10% to be clinically significant thus justifying our effect size of 0.1.

While we acknowledge the potential benefits of a larger sample size as recommended by Teare et al. [20], this initial feasibility study serves as a critical first step in understanding the recruitment landscape for our intervention as well as the feasibility of our protocol. The data obtained from this study will inform decision-making regarding the feasibility of a future multi-centre feasibility trial such as the resource considerations to achieve the larger sample size requirements.

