#### Exploratory outcome data analysis

The change in global impedance between the two groups will be summarised using descriptive statistics. This will include presenting the median values in each group (with interquartile ranges) without conducting hypothesis testing.The extubation failure rate: defined as the percentage of patients in each group that require reintubation within 72 h of their planned extubation.

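### The definitive-trial size of 2258 does not match the 10-point risk reduction said to justify it, because 0.1 was entered as a standardised shift rather than a risk difference

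*Protocol article*

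**What the plan says.** Under Study sample, the protocol article sizes a later definitive trial in G*Power. On the test: "This was based on a 2-group Wilcoxon-Mann-Whitney test". On the model and effect: "We assumed a logistic distribution for the dependent variable (extubation failure rate) in this future trial, with an effect size of 0.1". Alpha is 0.05 with no sidedness given, power is 0.80 and allocation is 1:1. The result: "This calculation suggested a total sample size of 2258 patients (1129 per group) would be required, indicating the need for a multi-centre trial".

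The same section then explains the effect size: "we would consider an absolute risk reduction in extubation failure rate of 10% to be clinically significant thus justifying our effect size of 0.1". It cites a mean failure rate of 15.7% across all critical care patients. It adds that the rate in acute respiratory failure is probably higher and poorly defined, and gives no figure for it.

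Under Exploratory outcome data analysis, extubation failure is "defined as the percentage of patients in each group that require reintubation within 72 h of their planned extubation", so each patient either fails or does not.

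**The concern.** Two different quantities share the number 0.1. In a Wilcoxon-Mann-Whitney calculation with a logistic parent distribution, the effect size is a shift in the mean of a continuous variable, measured in standard deviations. The article's justification is a difference between two proportions. The two are not interchangeable, and a logistic parent does not describe a binary outcome.

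At stake is the only sample size the article gives for a definitive trial. A reader planning or funding that trial would take 2258 as the price of detecting a 10-point reduction. If the true requirement is a few hundred, a practicable trial could look out of reach, or many more patients could be enrolled than the stated target effect calls for.

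**Working it through.** **Inputs from the article.** Effect size 0.1, alpha 0.05 (sidedness not stated), power 0.80, 1:1 allocation, logistic parent, control risk 15.7%, target reduction 10 points, stated result 1129 per group (2258). **Assumed here:** every control risk other than 15.7%.

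**Step 1: reproduce 2258.** The usual method takes the two-sample t-test and scales the sample size by the asymptotic relative efficiency of the rank test, which is π²/9 = 1.0966 for a logistic parent.

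Normal approximation, one-sided: n = 2 × ((1.645 + 0.842)/0.1)² / 1.0966 = 1236.5 / 1.0966 = 1127.6, so 1128 per group.

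The noncentral t version uses effective total N = 2n × 1.0966, df = N − 2 and noncentrality 0.1 × √(N/4):
- One-sided: 1128 per group gives power 0.7999 and 1129 gives 0.8003. The answer is 1129 per group, 2258 in total, an exact match.
- Two-sided: 1433 per group, 2866 in total. No match.
- Normal, uniform, Laplace and minimum-efficiency parents give 2592, 2476, 1650 and 2864 one-sided, and 3290, 3142, 2096 and 3636 two-sided. None matches.

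So 0.1 was entered in SD units and the test was one-sided. With a two-sided 5% test and the same inputs, 1129 per group has 70% power.

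**Step 2: what a 10-point reduction is in SD units.** For a binary outcome, d = 0.10 / √{[p₁(1−p₁) + p₂(1−p₂)]/2}. This is 0.33 at 15.7% v 5.7%, 0.25 at 25% v 15% and 0.20 at 50% v 40%. None of the control risks examined brings it near 0.1. Conversely, d = 0.1 is a difference of about 3.5 points from a 15.7% control risk and 5.0 points from 50%.

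**Step 3: size for the stated effect.** Two-sided 5%, 80% power, pooled variance under the null, no continuity correction, with p̄ = (p₁+p₂)/2:

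n = {1.960 √[2p̄(1−p̄)] + 0.842 √[p₁(1−p₁) + p₂(1−p₂)]}² / 0.10²

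At 15.7% v 5.7%, p̄ = 0.107 and n = (0.8568 + 0.3631)² / 0.01 = 148.8, so 149 per group.

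| Control v treated | Source of control risk | Per group | Total | 2258 ÷ total | Two-sided power at 1129 per group |
|---|---|---|---|---|---|
| 15.7% v 5.7% | article | 149 | 298 | 7.6 | >99.99% |
| 20% v 10% | assumed | 199 | 398 | 5.7 | >99.99% |
| 25% v 15% | assumed | 250 | 500 | 4.5 | >99.99% |
| 30% v 20% | assumed | 294 | 588 | 3.8 | 99.98% |
| 40% v 30% | assumed | 356 | 712 | 3.2 | 99.88% |
| 50% v 40% | assumed | 388 | 776 | 2.9 | 99.77% |
| 55% v 45% | assumed (largest n) | 392 | 784 | 2.9 | 99.75% |

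A continuity correction raises the totals to 338 at 15.7% and 824 at 55% (ratios 6.7 and 2.7). A one-sided test lowers them to 236 and 618 (ratios 9.6 and 3.7). At 1129 per group, the difference detectable with 80% two-sided power from 15.7% is about 4.0 points.

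**The case against.** Several points on the other side are sound.

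- **The software's arithmetic is right.** For the inputs entered, 2258 is correct. The fault lies in the effect measure and the model.
- **The undeclared one-sided test does not cause the inflation.** A reader might infer that it does. It lowers the total (2258 against 2866) and so partly offsets the effect-size mix-up. The article does not commit to a two-sided test either, so the missing sidedness is a secondary reporting gap.
- **The 7.6-fold end is the least applicable.** It rests on 15.7% in all critical care patients, and the article expects a higher rate in its own population. At assumed risks of 25% to 55% the ratio is 4.5 to 2.9.
- **Nothing in the present trial depends on 2258.** A reader might infer that this trial is mis-sized. The article describes the target of 30 as pragmatic and resource-driven, no endpoint or progression criterion uses the larger figure, and recruitment has closed.
- **The next stage is not sized from it.** A reader might also infer that 2258 drives resources for the next study. That study is a multi-centre feasibility trial, and the Discussion leaves powering of the definitive trial until after it. The remark under Study sample about larger sample size requirements follows a sentence on the pilot-size recommendation (120 to 200 in total) and more naturally refers to that.
- **The multi-centre conclusion survives.** At this site's set upper limit of 30 patients a year, 298 patients would take at least 298/30 ≈ 10 years and 588 at least 588/30 ≈ 20.

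These points limit the consequence. None reconciles 0.1 SD with a 10-point risk difference, which the article explicitly equates.

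**Conclusion.** The point holds as a moderate one. The printed 2258 is the size for a 0.1 SD shift in a continuous logistic variable, tested one-sided at 5%. It is not the size for the 10-point reduction in a binary outcome that the article gives as its justification. For that effect, a two-sided comparison of proportions at 80% power needs 298 patients in total at 15.7% and at most 784 at any baseline, so 2258 is about 2.9 to 7.6 times too large. With 1129 per group, power for 10 points exceeds 99.7% at every rate examined.

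The multiple depends on the control risk (only 15.7% comes from the article) and on the two-sided convention without continuity correction. The direction does not: under every variant tried, 2258 is at least 2.7 times what the stated effect requires. The documents do not support treating this as a flaw in the 30-patient trial or as grounds to doubt the need for several centres.

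**What to change.** Under Study sample, replace the Wilcoxon-Mann-Whitney calculation with a comparison of two proportions for a 10-point absolute reduction, and state whether the test is one- or two-sided. Tabulate total size over a range of control risks, marking which come from the literature and which are assumed; two-sided, for example, 298 (15.7%), 398 (20%), 500 (25%), 588 (30%) and 712 (40%). Note that 10 points off 15.7% is a relative reduction of 10/15.7 = 64%, so that readers can judge whether the smallest total is realistic. Delete 2258, the logistic assumption and the link between the 10-point reduction and an effect size of 0.1.

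If the need for a multi-centre trial is argued from the new totals, describe 30 a year as an upper limit, which makes the resulting duration a minimum. The cost is text only: no data, analysis or progression criterion of the present trial changes.

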### Eligibility criteria

Patients will be eligible to participate if (1) they are aged 18–80 years at the time of recruitment for the study, (2) they have been ventilated for ≥ 48 h with respiratory failure, (3) they are ready for a planned extubation in the opinion of the treating clinician (e.g. the patient is established on pressure support ventilation, FiO_2_ ≤ 0.4, PEEP ≤ 10 cm H_2_0, with a respiratory rate ≤ 20), (4) they have minimal secretions, (5) they are neurologically intact (in the opinion of the treating clinician, the patient is unlikely to fail extubation due to their neurological status), (6) they are cardiovascularly stable (systolic blood pressure ≥ 70 mmHg, heart rate ≤ 150 bpm) and (7) written informed consent has been given.

Exclusion criteria include the following:

#### Medical contraindications

Severe type II respiratory failure (PaCO_2_ ≥ 12 kPa)Severe acidosis ([H^+^] ≥ 80 nmol/L)Chronic respiratory disease limiting functional capacity (MRC breathlessness grade IV or V)Severe heart failure (NYHA grade III or IV)GCS score ≤ 12Cardiovascular instability (systolic blood pressure ≤ 69 mmHg or heart rate ≥ 151 bpm)Pulmonary embolismLife expectancy ≤ 3 months

#### Contraindications to EIT

Implantable cardiac devicesInternal neurostimulatorUnstable spinal fracture or spinal cord injuryBody mass index > 50 kg/m^2^Skin lesions or dressings at the electrode belt sitePregnancy or lactationIntercostal Chest Drain (at the treating clinician’s discretion)

